### Randomization

Patients will be randomly assigned to receive either conventional physical therapy (conventional group) or exercise training intervention using a cycle ergometer associated with conventional physical therapy (intervention group). Randomization sequence is going to be created by using the website www.randomization.com, with a 1:1 allocation ratio using blocks of 10 participants.

To ensure the confidentiality of randomization sequence, the sequence will be generated by an assessor who has not participated in data collection or study design and will be contacted by telephone only after the participant has been included in the study and is ready to start the protocol.

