**Methods/Design:**

A single-blind randomized controlled trial (the MoVe ICU study) will be conducted to evaluate and compare the effects of early rehabilitation using a bedside cycle ergometer with conventional physical therapy on the muscle morphology of the knee extensors and diaphragm in critical ill patients receiving MV. A total of 28 adult patients will be recruited for this study from among those admitted to the intensive care department at the Hospital de Clínicas de Porto Alegre. Eligible patients will be treated with MV from a period of 24 to 48 h, will have spent maximum of 1 week in hospital and will not exhibit any characteristics restricting lower extremity mobility. These subjects will be randomized to receive either conventional physiotherapy or conventional physiotherapy with an additional cycle ergometer intervention. The intervention will be administered passively for 20 min, at 20 revolutions per minute (rpm), once per day, 7 days a week, throughout the time the patients remain on MV. Outcomes will be cross-sectional quadriceps thickness, length of fascicle, pennation angle of fascicles, thickness of vastus lateralis muscle, diaphragm thickness and excursion of critical ICU patients on MV measured with ultrasound.

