### Patients

This is a single-blind RCT that is going to be conducted by the intensive care and physiotherapy departments at the Hospital de Clínicas de Porto Alegre (HCPA)–Universidade Federal do Rio Grande do Sul (UFRGS). Patients of both genders aged ≥18 years will be recruited from among those admitted to the HCPA ICU and undergoing MV from 24 to 48 h after transfer from the emergency department or wards, no more than 1 week after admission. Exclusion criteria will include neuromuscular diseases causing motor deficits, such as strokes, multiple sclerosis, amyotrophic lateral sclerosis, myasthenia gravis and Guillain-Barré syndrome. Patients will also be excluded in the event of the following: extubation less than 48 h after enrollment on the study; hemodynamic instability (norepinephrine > 0.5 μg/kg/min for arterial blood pressure > 60 mmHg); complications during the protocol such as pneumothorax, deep vein thrombosis or pulmonary embolism; Shilley catheter in the femoral vein; reintubation; delayed weaning (3 failed spontaneous ventilation tests); body mass index (BMI) > 35 kg/m^2^ [2]; or emergence of eschar in the calcaneus area during the protocol.

For sample selection, an assessor is going to conduct a daily search for potential trial participants using the hospital computer system. Then, electronic medical records will be reviewed by patient identification, medical diagnosis, and current medical condition in order to assess patients for eligibility. The next of kin to each eligible patient will be approached for study enrollment. Those who agreed to participate will be asked about the laterality of the patient and will be required to provide written consent.

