### Interventions

Conventional (chest and motor) physical therapy is going to be performed by staff physical therapists who have at least 2 years of experience in the care of critically ill patients. All patients will receive 30-min physical therapy sessions twice daily (morning and afternoon). The protocol consists of passive diagonal movements based on the proprioceptive neuromuscular facilitation (PNF) stretching technique for the upper and lower extremities (two sets of 10 repetitions per set of each diagonal movement bilaterally) and manual bronchial hygiene techniques, such as chest compression-vibrations, resuscitation maneuvers with an Ambu® bag, Ambu, Ballerup, DK), and suction of secretions when necessary.

The intervention group (IG), in addition to conventional physical therapy, is going to undertake passive cycling exercise training for the lower extremities using a bedside cycle ergometer (Flexmotor; Cajumoro, São Paulo, SP, Brazil). For the cycling exercise, patients will be in the supine position with the head of the bed elevated to 30 °. Each patient will perform passive cycling movements at 20 rpm for 20 min once daily, 7 days a week, in the afternoon prior to conventional physical therapy, until extubation or day 7 of the protocol. The protocol will be discontinued if hemodynamic instability occurs (requiring norepinephrine >0.5 μg/kg/min for a mean arterial pressure (MAP) >60 mmHg), systolic blood pressure (SBP) >200 mmHg, heart rate <40 beats/min and persistent peripheral arterial saturation < 88 % or if performing tracheostomy is required.

Before and after each exercise session, the cycle ergometer will be cleaned following the cleaning procedures adopted in the ICU and the criteria established by the hospital infection control committee. Before starting the cycling exercise, all procedures will be briefly explained to the patient regardless of their level of consciousness or sedation. To minimize contact with the device, the heel region is going to be covered with sterile gauze and secured with adhesive tape so that the ankle joint will be close to a 90 ° angle. The passive cycling movements generate alternating extension and flexion of the knee and hip, bilaterally, for 20 consecutive minutes. All procedures will be performed under the supervision of one of the investigators.

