## Trial status

Recruiting since May 2013.

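### A single fixed block length of 10, disclosed during recruitment in one ICU where allocation is visible, weakens allocation concealment: about 3.6 of 28 assignments can be deduced in advance

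*Protocol article*

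**What the plan says.** Under Randomization, the protocol article specifies allocation "with a 1:1 allocation ratio using blocks of 10 participants". It states one length, no variation of length and no stratification factor. The safeguard follows in the same section: "To ensure the confidentiality of randomization sequence, the sequence will be generated by an assessor who has not participated in data collection or study design". That person "will be contacted by telephone only after the participant has been included in the study and is ready to start the protocol".

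Other sections bear on how well this works:

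- **Status.** Trial status reads "Recruiting since May 2013", so the block length was disclosed in an article that describes recruitment as open.
- **Setting and size.** Patients are "recruited from among those admitted to the HCPA ICU" (Patients), and the Abstract gives a total of 28.
- **Visibility.** Under Interventions, only the intervention group uses the bedside ergometer, and "All procedures will be performed under the supervision of one of the investigators". Under Assessment, the ultrasound examiner is blind to group. No one else is described as blind.
- **Order of steps.** Under Patients, an assessor searches the hospital system daily and reviews diagnosis and current condition. The next of kin of each eligible patient are then approached. The telephone call comes later.

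**The concern.** The procedure protects the list from being read. It cannot protect against inference from allocations already made. Once five patients in a block of 10 have gone to one arm, every remaining patient in that block goes to the other. With one fixed, disclosed length and allocation visible in one unit, such an observer needs only a running count.

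This matters because the patient's condition is reviewed, and inclusion settled, before the call. If the person judging eligibility knew the next assignment, who enters each arm could be influenced at those points. With 14 per arm, a few such patients can shift baseline prognosis. The blinded ultrasound examiner guards against biased measurement, not against a difference in who was enrolled.

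**Working it through.** **Inputs.** Block length 10, 1:1 (Randomization). Total 28 (Abstract), 14 per group, effect 1.2, 5% significance, 85% power (Sample size calculation). Assumptions: the effect is read as 1.2 SD although the article words it in standard errors; the test is two-sided; the observer knows the block length and all past allocations.

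**1. The plan's own figure.** For a two-sample t test at d = 1.2, power is 83.5% with 13 per group and 86.3% with 14, so 14 per group is reproduced under the SD reading.

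**2. Certain assignments in a complete block.** There are C(10,5) = 252 equally likely blocks. Exactly k assignments are certain when the last k are alike and the one before them differs, which happens in 2 × C(9−k, 4) blocks.

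| k certain | Blocks | Probability |
|---|---|---|
| 1 | 140 | 55.6% |
| 2 | 70 | 27.8% |
| 3 | 30 | 11.9% |
| 4 | 10 | 4.0% |
| 5 | 2 | 0.8% |

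Mean = (140 + 140 + 90 + 40 + 10)/252 = 420/252 = 1.67. The minimum is 1.

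**3. The third block.** Since 28 = 10 + 10 + 8, this block stops at its eighth place and its last two places are not used. A run of k certain places then contributes k − 2 if k is at least 3, and otherwise none. Mean = (30×1 + 10×2 + 2×3)/252 = 56/252 = 0.22. In 210/252 = 83.3% of cases no assignment is certain.

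**4. Whole trial.** 2 × 1.667 + 0.222 = 3.56 of 28, or 12.7%. The minimum is two (patients 10 and 20). If enrolment ran on to 30, for example to replace exclusions, the figure would be 3 × 1.667 = 5 of 30.

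**5. Probable guesses.** Always guessing the arm with more places left is right on average 6.53 times in a complete block and 4.81 times in the truncated one: (2 × 6.53 + 4.81)/28 = 63.8%, against 50% with no information. In 20,000 simulated lists with random lengths of 8, 10 or 12, guessing the arm that is behind is right about 17.95 times in 28 (64.1%), against 17.87 for fixed blocks of 10.

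**6. Possible consequence.** The article gives no selection effect, so this is an assumed range. Suppose prognosis at the certain places is shifted by δ SD in favour of the intervention. The expected bias is about 3.56 × δ/14 = 0.25δ: 0.13 SD for δ = 0.5 and 0.25 SD for δ = 1.0. Simulated type I error with no true effect is about 6.1% and 9% respectively, against 5%.

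**7. Price of varied lengths.** In simulated lists of 28 with lengths 8, 10 or 12, the arms differ by 0, 2, or 4 or more in 62%, 36% and 2% of lists. Fixed blocks of 10 never differ by more than 2 at 28 patients. Power at 1.2 SD is 86.3% for 14:14, 86.2% for 15:13 and 85.6% for 16:12.

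**The case against.** A reader might infer that the fixed block defeats the stated confidentiality and that the closing assignments of every block are known. The article does not support that. The third block normally yields nothing certain, a complete block most often yields only one certain assignment, and about 87% of assignments are never certain. The list is held by someone outside data collection and design, and it stays hidden.

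A reader might also infer that families could be approached selectively. As written, there is no such discretion: the next of kin of each eligible patient are to be approached. Exploiting foreknowledge would need latitude in judging eligibility or a departure from that rule. Nor does the article say that the screening assessor follows allocations, that the supervising investigator enrols patients, or that recruiting staff know the block length. A condensed article may leave such operational detail to the full protocol.

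Two further objections stand. Ten is already a fairly long block for 28 patients: fixed blocks of 4 would make about 7 × 1.33 = 9.3 assignments certain. And varying the lengths does not lower the average rate of correct guessing, so bias acting through probable guesses would remain.

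These arguments limit the size of the point but do not remove it. The block scheme is positively stated, and telephone release cannot prevent deduction from past allocations.

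**Conclusion.** The point holds as a cheap improvement with limited gain. One fixed block length, disclosed during recruitment in a single ICU with visible allocation, weakens concealment for about 3.6 of 28 patients (13%), always including patients 10 and 20. The risk is structural: nothing in the article shows that foreknowledge was available to those who enrol, or was used.

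The count rests on enrolment stopping at 28 and on an observer who knows the length and every past allocation. The bias figures rest on an assumed selection effect, and the power figures on reading the effect as 1.2 SD. The article gives no enrolment count. If only the truncated third block remained to be filled, just 0.22 assignments would be expected to be certain and a change would achieve little.

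**What to change.** If unallocated slots remain, the same independent list holder should generate them with randomly varied block lengths, for example 8, 10 and 12. Neither the lengths nor the set they are drawn from should reach recruiting or treating staff until the last patient is randomised. If the set were known, a block still unbalanced after 10 patients would have to be one of 12, and its end could again be deduced. The scheme can be reported afterwards.

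The cost is one new list for the remaining slots, with no change to the sample size. The downside is a roughly 2% chance of an arm difference of 4 or more (for a full list of 28), at a power cost below one percentage point at 16:12. The gain is the removal of certain foreknowledge only; correct guessing stays near 64%.

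If recruitment is too advanced for a new list, the sponsor can state whether those who judged eligibility and approached families were unaware of earlier allocations and of the position within the block.

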### Statistical analysis

Continuous variables will be expressed as mean and standard deviation or standard error, or as median and interquartile range. Categorical variables will be expressed as absolute and relative frequencies. The Shapiro-Wilk test will be used to test the normality of distribution, and Levene’s test will be used to assess homogeneity of variance for all group comparisons. Student’s *t* test for independent samples will be used to compare means between groups, and the Mann–Whitney test will be used to compare medians between groups. Qualitative data will be analyzed using the chi-square test or Fisher’s exact test when at least 25 % of the cells exhibited the expected frequency <5. To evaluate the intra-group effects, the group and subgroups (septic versus non-septic) in changing muscle parameters, the model of Generalized Estimating Equations (GEE) will be performed with Bonferroni adjustment. Analysis of covariance (ANCOVA) will be used to control for confounding factors such as BMI, duration of protocol and duration of MV. Statistical analysis will be performed using SSPS, version 17.0 (SSPS Inc., Chicago, IL, USA). The level of significance is going to be set at 5 % (*p* ≤ 0.05).

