### Outcomes

The primary endpoint with respect to the efficacy of passive leg cycle exercise in preserving muscle morphology may be the difference in cross-sectional thickness of the dominant quadriceps muscle from initial to final assessment between groups. Secondary efficacy endpoints may include changes in muscle architecture parameters, such as vastus lateralis fascicle length, PA, muscle thickness, and diaphragm thickness and excursion. We will also assess length of ICU and hospital stay, duration of MV, successful extubation, and incidences of patient death. In addition, septic (requiring vasoactive drugs) and non-septic patients will be compared in terms of primary and secondary outcomes.

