### Sample size calculation

The sample size calculation is based on a pilot study with 10 patients. To achieve an effect size of 1.2 standard errors between groups as cross-sectional thickness of the quadriceps muscle, significance level of 5 % and power of 85 % and 2 repeated measures (initial and final), the sample size estimated by the (WinPepi, http://www.brixtonhealth.com/pepi4windows.html) 11.43 statistical program was of 14 patients in each group.

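### No single primary analysis is named for the change in quadriceps thickness, and the ANCOVA lists two post-randomisation durations but not initial thickness

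*Protocol article*

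**What the plan says.** - **Endpoint** (protocol article, Outcomes): the primary endpoint is "the difference in cross-sectional thickness of the dominant quadriceps muscle from initial to final assessment between groups". The same section lists duration of MV as a further outcome.
- **Baseline** (Assessment): the first ultrasound is done on the first study day. The same blinded examiner does the second, on day 7 or 24 h after extubation.
- **Tests** (Statistical analysis): after Shapiro–Wilk and Levene checks, a Student's t "test for independent samples will be used to compare means between groups", with Mann–Whitney for medians. GEE with Bonferroni adjustment is used for intra-group, group and septic-subgroup effects on changing muscle parameters. ANCOVA is used to control for "confounding factors such as BMI, duration of protocol and duration of MV".
- **Sample size** (Sample size calculation): the inputs are an "effect size of 1.2 standard errors between groups as cross-sectional thickness of the quadriceps muscle", with "power of 85 % and 2 repeated measures (initial and final"), and the result is that the "statistical program was of 14 patients in each group".

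No section says which test gives the primary p-value, and initial thickness is not a named covariate.

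**The concern.** Two weaknesses meet in one section.

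**Choice of test.** The t test or Mann–Whitney test, the GEE group effect and the ANCOVA can each be applied to the primary endpoint. If the choice is made after the results are seen, the 5 % level no longer holds.

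**Choice of covariates.** Initial thickness is collected at enrolment and is likely to predict final thickness well, yet it is not listed. Two listed variables are fixed only after randomisation: the protocol runs to extubation or day 7, and duration of MV is an outcome of the trial. If cycling alters either, adjusting for it can remove or distort part of the treatment effect. That is not confounder control, because randomisation already makes the groups comparable at the start.

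With 28 patients, both the lost precision and the freedom of choice matter.

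**Working it through.** **1. The plan's own figure.** Inputs from Sample size calculation: effect 1.2 (read as SDs), alpha 5 % (two-sided assumed), power 85 %.

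- Normal approximation: n = 2(1.960 + 1.036)² / 1.2² = 12.5, so 13 per arm.
- Noncentral t: power is 83.5 % at 13 and 86.3 % at 14, so 14 per arm.

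The stated 14 reproduces. Read literally as standard errors, 1.2 would give only about 22 % power, so SDs are evidently meant.

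**2. Precision from adjusting for initial thickness.** Assume equal SDs (σ) at the two times and correlation rho. The document gives no rho, so 0.5 to 0.9 is shown.

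- Variance of the group difference in change: (2/n) × 2σ²(1 − rho).
- Variance of the baseline-adjusted difference: (2/n) × σ²(1 − rho²) × [1 + 1/(2n − 4)]. The last factor is the price of estimating the slope; at n = 14 it is 1 + 1/24 = 25/24.
- Ratio: (1 + rho)/2 × 25/24.

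Power uses a noncentral t with 25 degrees of freedom and noncentrality 1.2 × √(14/2) / √ratio, taking 1.2 as SDs of change. The change-score comparison has power 86.3 %.

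| rho | (1 + rho)/2 | × 25/24 | equivalent extra patients (1/ratio − 1) | power at 14 per arm |
|---|---|---|---|---|
| 0.5 | 0.75 | 0.781 | 28 % | 93 % |
| 0.7 | 0.85 | 0.885 | 13 % | 90 % |
| 0.8 | 0.90 | 0.938 | 7 % | 88 % |
| 0.9 | 0.95 | 0.990 | 1 % | 87 % |

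Simulated variance ratios agree with the third column to within about 0.01.

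**3. Error rate when the smallest p-value is taken.** Simulation under no effect: 14 per arm, 10,000 trials at each of rho 0.5, 0.7, 0.8 and 0.9, bivariate normal data. The ANCOVA of change carried three noise covariates. GEE was a group-by-time Wald test with an uncorrected sandwich standard error.

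| Analysis | Rejections at 5 % |
|---|---|
| t test on change alone | 4.8–5.2 % |
| ANCOVA of change, no baseline, alone | 4.7–5.1 % |
| GEE alone | 6.8–7.1 % |
| Better of t test and ANCOVA | 6.1–6.7 % |
| Best of t test, GEE and ANCOVA | 7.7–8.3 % |
| The same three plus Mann–Whitney | 8.0–8.6 % |
| ANCOVA of final on group and initial thickness | 4.9–5.1 % |

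Three independent tests would give 1 − 0.95³ = 14.3 %. These tests are strongly correlated, so the inflation is much smaller.

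**4. The duration covariates.** The noise covariates in step 3 are unrelated to group and outcome, so the simulation does not measure bias from adjusting for durations that treatment may change. The document gives no figure from which to size it.

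**The case against.** **GEE may be the intended main model.** It is the only method tied to changing muscle parameters, and the sample size assumes two repeated measures. The t test sentence names no endpoint and could serve baseline characteristics or length of stay; the ANCOVA can be read as a supplement. This is a fair reading, so calling the three methods rival primary tests goes too far. But the text does not say that GEE is primary.

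**Baseline is not ignored.** GEE uses initial thickness as the first of two measurements, and the covariate list is open-ended. Both points stand. With two time points, however, the GEE group-by-time effect behaves roughly like a change score, so it does not bring the gain in step 2. What is missing is baseline as a covariate, not baseline data.

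**An analysis of change is not wrong.** Under randomisation it is unbiased, and its t test holds about 5 %. Preferring ANCOVA is a matter of efficiency. This stands too.

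**An analysis plan may settle the ranking.** It may. But the article itself states the tests and names the covariates, and the inclusion of two post-randomisation durations is a stated choice.

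**Stronger readings that a reader might infer:**
- *Precision is free and large.* The large-sample ratio (1 + rho)/2 suggests 33 %, 18 % and 11 % more patients at rho 0.5, 0.7 and 0.8. At 14 per arm the figures are 28 %, 13 % and 7 %, and about 1 % at rho 0.9. The same examiner, a mapped scan site and a short interval make a high rho plausible.
- *Test selection alone gives 8 %.* Most of that excess comes from the uncorrected GEE standard error, which gives about 7 % by itself. The article does not specify the variance estimator, so this is an assumption.
- *The error rate reaches about 12 %.* That requires adding a t test on final values alone, but the Outcomes section defines the primary endpoint as change.

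**Conclusion.** The point holds in a limited form and should be acted on. The article names no single primary analysis for the change in quadriceps thickness. Its ANCOVA names two post-randomisation durations and leaves out initial thickness.

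The precision gain from adjustment runs from about 22 % of the change-score variance at rho 0.5 to about 1 % at rho 0.9. It rests on an assumed rho, equal SDs at the two assessments and 1.2 meaning SDs of change. The error rate from choosing among the listed tests is about 6–7 % for t test and ANCOVA, and about 8 % only if GEE is run with uncorrected sandwich errors.

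The duration covariates are the most concrete flaw in the wording, but their effect cannot be sized from the document. Nothing here shows that the planned change-score comparison is biased or invalid.

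**What to change.** - **Primary analysis.** Name one: a linear model of final quadriceps thickness on group and initial thickness (BMI optional), two-sided 5 %, reporting the adjusted difference with its 95 % CI.
- **Covariates.** Leave duration of protocol and duration of MV out of this model.
- **Other methods.** Label the t test or Mann–Whitney test and the GEE as supportive, and give the GEE a small-sample correction.
- **Timing.** Recruitment has run since May 2013 (Trial status), so record the choice in a dated amendment before any unblinded comparison.

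The cost is one degree of freedom and the amendment; no new data are needed. The model does not settle how patients without a final scan are handled, which has to be stated separately.

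### GEE is named for treatment and sepsis effects on muscle change with only 28 patients and no small-sample safeguard, and neither the deciding primary test nor the Bonferroni family is fixed

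*Protocol article*

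**What the plan says.** The Outcomes section of the protocol article makes the primary endpoint the between-group difference in change of dominant quadriceps thickness from the initial to the final assessment. It adds that "septic (requiring vasoactive drugs) and non-septic patients will be compared in terms of primary and secondary outcomes".

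The Sample size calculation section assumes "an effect size of 1.2 standard errors between groups as cross-sectional thickness of the quadriceps muscle", a "significance level of 5 % and power of 85" %, and "2 repeated measures (initial and final"). The resulting size "was of 14 patients in each group". The abstract agrees: "A total of 28 adult patients will be recruited".

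The Statistical analysis section names several methods that could apply to the primary endpoint:

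- Student's t test, or Mann–Whitney, for comparisons between groups.
- GEE for within-group, group and septic/non-septic effects on change in muscle parameters, where "the model of Generalized Estimating Equations (GEE) will be performed with Bonferroni adjustment".
- ANCOVA to control for BMI, duration of protocol and duration of ventilation.

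The significance level is 5 %. The section does not give the GEE covariance estimator, a small-sample correction, the reference distribution, the number of comparisons in the Bonferroni family, or which test decides the primary endpoint.

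**The concern.** The GEE sentence is the one tied to change in muscle parameters, and it includes the group effect, so it covers the primary endpoint. GEE inference rests on a large number of independent clusters. Here the clusters are the 28 patients, and fewer in any sepsis stratum. With so few, the uncorrected robust standard error is too small on average, and a normal or chi-square reference makes the p-value smaller still. Intervals are too narrow and false positives exceed the stated 5 %.

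Two ambiguities add to this. The t test and GEE can disagree on the same data, and no rule says which prevails. The Bonferroni adjustment is attached to the GEE analysis as a whole, without saying whether the single contrast on which the trial was sized is exempt. If it is not exempt, the planned power no longer applies.

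**Working it through.** **Inputs.** From the protocol: 14 per arm, two measurements per patient, 5 % level, 85 % power, effect 1.2. Assumed: two-sided testing; 1.2 meaning standard deviations of the analysed outcome (the text says standard errors, but 14 per arm reproduces only with SD); the uncorrected robust Wald test for GEE; normally distributed changes with equal variance; the stratum sizes shown below.

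**1. The protocol's own sample size.** For a two-sided t test the noncentrality is 1.2 × √(14/2) = 3.175 on 26 df. Power is 86.3 % at 14 per arm and 83.5 % at 13, so 14 is the smallest size reaching 85 %. The stated figure reproduces, at an unadjusted 5 %.

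**2. What the uncorrected robust Wald test becomes.** With two visits and a model containing group, time and their interaction, the interaction estimate is the difference in mean change. Its robust variance is the sum over arms of (divisor-n variance of change)/n. Fitting GEE to simulated trials confirmed this identity (largest difference in the test statistic about 4 × 10⁻¹⁵). With n per arm, the test therefore rejects when the ordinary two-sample |t| exceeds 1.96 × √((n−1)/n), so

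true level = 2 × P(t with 2n−2 df > 1.96 × √((n−1)/n)).

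| n per arm | cut-off on t | df | true level |
|---|---|---|---|
| 14 (whole trial) | 1.889 | 26 | 7.0 % |
| 10 (one stratum) | 1.859 | 18 | 7.9 % |
| 7 | 1.815 | 12 | 9.5 % |
| 5 | 1.753 | 8 | 11.8 % |
| 4 | 1.697 | 6 | 14.1 % |

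Simulation (400,000 trials per setting) gave 7.0 % at 14 vs 14, 9.4 % at 7 vs 7, and 12.4 % for an uneven stratum of 10 vs 4. Welch's t test on the same changes gave 4.9 % at 14 vs 14 and 4.6 % at 7 vs 7. For a within-group change, the corresponding level with n−1 df is 8.1 % at n = 14 and 12.0 % at n = 7.

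**3. Where the tests disagree.** At 14 per arm the t test needs |t| > 2.056 and the uncorrected Wald test |t| > 1.889. Any result between the two, that is a t-test p between 0.05 and 0.07, is significant under one and not under the other.

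**4. Bonferroni, if the primary contrast is in the family.** The protocol gives no number of comparisons k, so k = 2 and k = 4 are illustrations. All figures are at 14 per arm and 1.2 SD.

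| k | level per test | t-test power | uncorrected Wald power | true level of that Wald test |
|---|---|---|---|---|
| 1 | 5 % | 86 % | 90 % | 7.0 % |
| 2 | 2.5 % | 78 % | 84 % | 4.0 % |
| 4 | 1.25 % | 69 % | 77 % | 2.3 % |

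Keeping 85 % power with the t test would need 17 per arm at k = 2 and 19 at k = 4.

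**The case against.** The strongest reply is that the protocol never says the uncorrected robust Wald test will be used. A model-based or corrected variance may be specified in a full protocol or analysis plan that is not shown, and Student's t test, which is listed, holds its level at 14 per arm. This stands as a limit: the 7.0 % is conditional, and a reader may not infer that the primary p-value will be anti-conservative. It does not remove the point. The article itself chose a large-sample method for 28 patients, applied it to the group effect on change, and left it beside other tests without ranking them.

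A reader might also infer that a Bonferroni adjustment contradicts the 5 % level used for the sample size. It does not. Bonferroni can keep a family at 5 %, and the adjustment may be meant only for within-group and subgroup comparisons. There is a loss only if the primary contrast is inside the family. Nor can the 7 % inflation and the Bonferroni loss fall on the same primary test: with k = 2 the Wald test's true level is 4.0 %, below 5 %. If the Wald test is used, its own power column applies and the loss is smaller than for the t test.

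A single figure for sepsis, such as nearly 10 %, would be false precision. It needs 7 patients per arm in a stratum and applies to a treatment effect within that stratum. On the same even split, comparing change between septic and non-septic patients (14 vs 14) gives 7.0 %, and the three-way interaction over four cells of 7 gives about 8.2 % (24 df).

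Finally, nothing says that within-group tests will decide efficacy. The stated endpoint is a between-group difference.

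**Conclusion.** The point holds in conditional form and should be acted on. If GEE is run with the uncorrected robust Wald test, the nominal 5 % test of the primary between-group change has a true level of about 7.0 %, and a treatment effect within one sepsis stratum about 8 % to 14 % for 10 down to 4 per arm. Both rest on the assumed estimator, and the second also on stratum sizes that the protocol does not give. What needs no such assumption is that the deciding test and the Bonferroni family are not fixed. If the family includes the primary contrast, t-test power falls from 86 % to 78 % (two comparisons) or 69 % (four). That is an ambiguity with a conditional cost, not a contradiction.

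**What to change.** - Name one primary test: the between-group difference in quadriceps thickness change, at two-sided 5 %, outside any Bonferroni family.
- Use ANCOVA of final thickness on baseline thickness. Acceptable alternatives are a mixed model with Satterthwaite or Kenward–Roger degrees of freedom, or GEE with a small-sample-corrected sandwich variance and a t reference.
- Apply Bonferroni only to secondary and septic/non-septic comparisons, and list the comparisons in the family.
- Report within-group changes descriptively.

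The cost is a few sentences in the Statistical analysis section; no patients or procedures change. Intervals become slightly wider than under uncorrected GEE. For a t-based analysis of change at 14 per arm the ratio is 2.056/1.889 = 1.09, about 9 % wider.
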